#### Exclusion criteria

2.3.2

##### Exclusion criteria of the COPD group

2.3.2.1

(1)Patients cannot satisfy the COPD diagnostic criteria, or COPD patients in acute exacerbation;(2)COPD patients have other major lung diseases, such as bronchiectasis, bronchial asthma, pneumothorax, chest trauma, and lung tumors;(3)Patients have concomitant heart diseases;(4)Patients have serious concomitant diseases in major systems and could not control them effectively at present, such as major diseases in the nervous, respiratory, digestive, urinary, and hematological system;(5)Patients have mental diseases, history of drug abuse and alcohol dependence;(6)Patients are lactating or pregnant;(7)Patients are taking part in other studies.

##### Exclusion criteria of the healthy volunteers

2.3.2.2

(1)Participants have mental illness, history of drug abuse and alcohol dependence;(2)Participants are lactating or pregnant;(3)Participants are taking part in other studies.

### Recruitment procedures

2.4

All participants will be enrolled from the Third Affiliated Hospital of Zhejiang Chinese Medical University. Our study will be advertised on the Internet and on posters in hospitals. Researchers will explain the aim, benefits, and potential risks of the study to participants in details. After signing written informed consents, all participants will be assessed by researchers to determine whether they can be included based on the inclusion and exclusion criteria.

### Blinding

2.5

Due to the nature of an open-labeled trial, we will not blind the manipulators, participants, and outcome assessors, only blinded statistical analysis will be adopted by employing statisticians who are unaware of the study protocol.

### Experimental procedures

2.6

Participants will be requested to refrain from consuming stimulating drinks (eg, tea, alcohol, coffee) and smoking on the day for fNIRS examination. Besides, exercise and food will be forbidden within 1 hour before fNIRS examinations.

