##### Inclusion criteria of COPD patients

2.3.1.1

(1)Patients should satisfy the COPD diagnostic criteria, and the level of COPD is GOLD 2 or 3 according to results of pulmonary function testing;(2)Patients are in the stable phase of COPD;(3)35 ≤ age ≤ 75 years, gender is not limited;(4)Patients have clear consciousness and can communicate with researchers normally;(5)Patients can understand the study protocol and agree to sign written informed consents.

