##### Inclusion criteria for the healthy volunteers

2.3.1.2

(1)Healthy volunteers can provide a recent medical examination report, which can verify that they do not have major neurological, cardiovascular, respiratory, digestive, urinary, endocrine, and hematological diseases;(2)Age ≥20 years, gender is not limited;(3)Participants have clear consciousness and can communicate with researchers normally;(4)Participants can understand the study protocol and agree to sign written informed consents.

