Second, based on comparison upon the metabolic differences of the Heart and Lung meridians in healthy adults and COPD patients, it will verify whether fNIRS is validated as an add-on technique to assist diagnosis of specific diseases that affects oxygen metabolism in tissue, such as COPD. Previous studies revealed that low oxygen saturation could be detected in peripheral vessels in COPD patients.^[29–31]^ Similarly, based on the theory of meridian-viscera association in traditional Chinese medicine, pathological changes of internal organs will manifest in the external regions or acupoints that belongs to the diseased meridian, and this phenomenon is confirmed by a number of modern studies.^[32,33]^ Nevertheless, it remains unclear whether the distribution regions of the Lung meridians present with abnormal oxygen metabolism in relative to distribution regions of the other meridians or non-meridian paths, which will be verified by the findings of our study.

Third, various kinds of measures will be made to minimize the confounding factors that affect the tissue oxygen metabolism. In details, an experimental room with controlled temperature and humidity is set up and participants are asked to rest for a long period to adapt to the environment. All fNIRS examinations are performed at about the same period of the day. Meanwhile, stimulating food or drink, and exercise are restricted before fNIRS examinations. Fundamental physiological parameters will be measured before and immediately after fNIRS examinations, with the aim to eliminate the possibility that the change of oxygen metabolism is resulted from significant change of fundamental physiological parameters in normal state. Moreover, in order to minimize individual differences, the ratio of participant gender is controlled as 1:1 and the age between the COPD group and the healthy group will try to be matched as much as possible.

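### Smoking history is not among the factors used to choose healthy controls, so the per-site COPD–control difference in oxygen saturation, and the diagnostic claim built on it, are open to confounding by smoking

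*Protocol article*

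**What the plan says.** Section 2.6 (Experimental procedures) asks participants to abstain from tea, coffee and alcohol and from "smoking on the day for fNIRS examination". Smoking is not mentioned anywhere else in the article.

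The eligibility lists are written out item by item. For COPD patients, section 2.3.1.1 gives the diagnosis, GOLD 2 or 3, stable phase, "35 ≤ age ≤ 75 years, gender is not limited", ability to communicate, and consent. For healthy volunteers, section 2.3.1.2 begins "Healthy volunteers can provide a recent medical examination report" and goes on to absence of major disease, a minimum age of 20, ability to communicate, and consent. The exclusion lists name other substance-related histories ("Patients have mental diseases, history of drug abuse and alcohol dependence" for COPD; "Participants have mental illness, history of drug abuse and alcohol dependence" for healthy volunteers) but not smoking.

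The Discussion says that "various kinds of measures will be made to minimize the confounding factors that affect the tissue oxygen metabolism". It then lists room conditions, rest, a common time of day, limits on stimulants and exercise, physiological readings before and after, and balancing of the groups: "the ratio of participant gender is controlled as 1:1 and the age between the COPD group and the healthy group", the age matching being on a best-effort basis.

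Section 2.11 compares groups by an independent-samples t-test, or a nonparametric test if the data are skewed, and names no covariate. The primary outcome (2.7) is regional oxygen saturation at the Heart and Lung meridian sites. The COPD–control comparison is used to infer meridian-visceral specificity and to judge fNIRS as an aid to diagnosing COPD (Discussion and Conclusions).

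**The concern.** A same-day ban deals with acute exposure. It does nothing about a difference in habitual smoking between the groups, and a comparison of COPD patients with healthy people is one where such a difference is plausible. The protocol has identified smoking as something that can move the measurement, and has set out which factors it will balance, yet leaves smoking out of them.

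Two conclusions depend on the COPD–control difference. The diagnostic one is the more exposed: if the difference at a site partly reflects smoking, fNIRS would seem to separate COPD from health when it partly separates smokers from non-smokers. The specificity conclusion is exposed only to the extent that it is drawn from site-by-site group comparisons, which are the between-group tests the article names. The choice of controls cannot be undone at analysis: if the groups hardly overlap on smoking, adjustment has little to work with.

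**Working it through.** **1. Where smoking is and is not handled**

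| Place | Smoking |
|---|---|
| 2.6 Experimental procedures | No smoking on the examination day |
| 2.3.1.1 and 2.3.2.1 (COPD inclusion, exclusion) | Not mentioned |
| 2.3.1.2 and 2.3.2.2 (healthy inclusion, exclusion) | Not mentioned |
| Discussion, balancing of groups | Sex and age only |
| 2.11 Statistical analysis, between groups | Two-sample test, no covariate named |

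**2. Inputs**

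- From the article: 120 participants in a 1:1:1 ratio (2.2), so 120/3 = 40 per group; significance level 0.05 (2.11). Sidedness is not stated; two-sided is assumed.
- Not in the article, assumed: a gap in smoking prevalence between COPD patients and controls of g = 0.3 to 0.6, and a smoking effect on rSO2 at a site of b = 0.3 to 0.5 SD.

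The article gives no effect size, SD or power, so there is no sample-size figure to reproduce beyond the 40 per group.

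**3. Bias and false-positive rate at one site, with no true COPD effect**

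Bias in SD units = g × b. Noncentrality = bias / √(2/40) = bias / 0.2236. The false-positive rate is the two-sided rejection probability of the t-test with 78 degrees of freedom.

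| g | b | Bias (SD) | Noncentrality | False-positive rate |
|---|---|---|---|---|
| 0.3 | 0.3 | 0.09 | 0.40 | 6.8% |
| 0.3 | 0.5 | 0.15 | 0.67 | 10.2% |
| 0.6 | 0.3 | 0.18 | 0.80 | 12.5% |
| 0.6 | 0.5 | 0.30 | 1.34 | 26.3% |

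At g = 0 the rate is 5%. Wider assumptions widen the range: with g from 0.2 to 0.6 and b from 0.3 to 0.8, a normal approximation gives 5.8% to 57.4%.

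For scale, 40 per group detects (1.960 + 0.842) × 0.2236 = 0.63 SD with 80% power. A bias of 0.09 to 0.30 SD is 14% to 48% of that.

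**4. Which comparisons are exposed**

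Let smoking shift rSO2 by b_L at Lung sites and b_H at Heart sites.

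- Per-site COPD–control difference: bias g × b_L or g × b_H. Exposed.
- COPD–control difference in the within-person Lung-minus-Heart value: bias g × (b_L − b_H), which is zero if b_L = b_H. Section 2.6.2 has all four sites recorded at the same time in the same person, so this contrast can be computed. Section 2.11 does not name it.
- Moxibustion comparison in the healthy intervention group: within person, so a stable smoking effect common to the sites largely cancels.

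**The case against.** The strongest reply is that this is a condensed article. Table 1 (the assessment schedule) and the case report forms are not available, and a separate analysis plan may exist. Recording of smoking history and covariate adjustment may well be provided for there, so the article cannot be faulted for omitting them. That stands. What remains is that the article does state its eligibility lists and balancing factors, and smoking is in neither.

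A second reply is that the meridian question is about Lung versus Heart, and a smoking effect shared by neighbouring forearm sites cancels within a person. That also stands. A reader might infer that no COPD–control finding could be attributed to the Lung meridian; the documents do not support that, because they give no reason why smoking should act differently at the Lung and Heart sites.

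Third, the controls are unrestricted on smoking only. They need a medical report ruling out major respiratory and cardiovascular disease, among others, and are roughly balanced on age and sex. One might go on to suspect undetected airflow obstruction among controls who smoke, but the article does not say what the report contains, and such cases would tend to shrink the COPD–control difference rather than create one.

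Fourth, the Discussion calls the study an exploratory pilot and concedes that individual differences may remain. This tempers the weight of the point. It does not answer a between-group imbalance that control selection could reduce.

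**Conclusion.** The point holds in a limited form. A factor that the protocol itself treats as affecting the measurement is left out of its stated eligibility and balancing rules, and the stated between-group test does not adjust for it. The per-site COPD–control difference in rSO2 and the diagnostic add-on conclusion are confounded if smoking history differs between the groups. The within-person Lung-versus-Heart contrast and the moxibustion comparison are largely protected, provided the smoking effect is similar across forearm sites.

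The size is unknown. The figures of 0.09–0.30 SD and about 7–26% false positives per site follow from assumed prevalence gaps and effects, and show only that the problem need not be trivial with 40 per group. That the COPD group smokes more is plausible but is not stated, so the direction of the bias is not established by the article either.

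Two further inferences are not supported. A reader might think that same-day abstinence means very different abstinence times for morning and afternoon examinations, but the Discussion says that examinations take place at about the same time of day. Mechanisms such as carboxyhaemoglobin misleading the oximeter, or lasting microvascular damage, have no basis in the document, and the point does not need them.

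**What to change.** 1. Record smoking status (never, former, current) and pack-years at screening in all groups, unless the full protocol or case report form already does.
2. Add smoking category to sex and age as a factor in choosing the 40 healthy controls, and say so where the balancing rule is stated.
3. Adjust the COPD–control comparison of rSO2 for smoking category.
4. Base the meridian-specificity claim on the group-by-meridian contrast: the COPD–control difference in the within-person Lung-minus-Heart value. Keep the per-site differences, adjusted for smoking, for the diagnostic question.

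Cost: two questions on the case report form, a change to the stated balancing rule and to section 2.11, and somewhat slower recruitment of controls who smoke or used to smoke. If smoking categories overlap poorly between the groups, adjustment will lose some precision.

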#### fNIRS examination environment

2.6.1

An experimental room will be set up for fNIRS examinations. The temperature for the examination environment will be controlled within 24°C ± 1°C. The relative humidity will be controlled between 30% and 50%. There is no direct sunlight and obvious air convection in the room.

#### Procedures for the fNIRS examinations and moxibustion

2.6.2

A 4-channel Oximeter (INVOS 5100C, Somanetics Corp., Troy, MI) will be used to detect the metabolic property of the Heart and Lung meridians. Before fNIRS examinations, all participants will stabilize for 15 minutes. They will also be requested to keep normal breathe, maintain still, and avoid movement of limbs during fNIRS measurement. After ripping adhesive tapes, the fNIRS probes will be attached to corresponding measurement sites synchronously. Oxygen saturation of corresponding regions along the Heart and Lung meridians will be monitored.

(1)Healthy control group and COPD groupThe fNIRS probes will be attached to 4 measurement sites synchronously (as shown in Fig. 2) to monitor oxygen saturation for 10 minutes, including acupoint HT3 and HT7 and of the Heart meridian, acupoint LU5 and LU9 and of the Lung meridian.(2)Healthy intervention groupMoxibustion will be performed in the Heart meridian and Lung meridian, respectively. The washout period between the 2 moxibustion sessions is more than 1 day. The procedures for intervention and the measurement places of the fNIRS probes are displayed in Figure 3.

1)Moxibustion in the Heart meridian: a moxa stick is ignited and inserted into a homemade holder to adjust appropriate height and angle, moxibustion is applied at acupoint HT3 of the Heart meridian for 15 minutes. The fNIRS probes will be attached to 3 measurement sites during moxibustion, including the midpoint of the Heart meridian along the left forearm (i.e. the midpoint between HT7 and HT3), the midpoint of the Lung meridian along the forearm (i.e. the midpoint between LU5 and LU9), and LU5 of the Lung meridian. The procedures for intervention and the measurement places of the fNIRS probes are shown in Figure 3A. The measurement time points consist of 5 minutes before moxibustion, 15 minutes during moxibustion, and 5 minutes after removing moxibustion.2)Moxibustion in the Lung meridian: moxibustion is applied at acupoint LU5 of the Lung meridian. The moxibustion procedure, fNIRS examinations and assessment time points are consistent with 1). The fNIRS probes will monitor oxygen saturation in 3 measurement sites synchronously during moxibustion, including the midpoint of the Lung meridian along the forearm (ie, the midpoint between LU5 and LU9), and the midpoint of the Heart meridian along the left forearm (ie, midpoint between HT3 and HT7, and HT3 of the Heart meridian. The procedures for intervention and the measurement places of the fNIRS probes are displayed in Figure 3B.

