### Study design

2.1

This study is designed as a prospective and clinical controlled trial. Eligible participants will be divided into the COPD group, healthy control group, and healthy intervention group. The study flowchart is presented in Figure 1 and the schedule for participant screening, interventions, and outcome assessments is shown in Table 1. The report of this protocol will strictly follow the guideline of the Standards for Reporting Interventions in Clinical Trials of Acupuncture.^[14]^

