### Sample size calculation

2.2

This study is a clinical trial that aims to measure the biological characteristics of meridians in COPD patients and healthy adults. Compared with common clinical trials that intend to evaluate the effectiveness of a specific therapy, there is no consensus on the standardization of sample size estimation for this kind of study. Thus, the sample size estimation is mainly according to similar trials^[15,16]^ and our preliminary study.^[12]^ Finally, the total number of participants is 120, and they will be divided into the COPD group, healthy control group, and healthy intervention group in a 1:1:1 ratio.

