### Data collection and statistical analysis

2.11

SPSS 17.0 for Windows (SPSS Inc., Chicago, IL) will be used to perform statistical analysis. For data expression, numeric data in normal distribution will be presented as mean and standard deviations, and data in skewed distribution will be presented as median and interquartile ranges. For statistical analysis methods, change in continuous variables at different time points will be analyzed by repeated measures analysis of variance. The changes within the groups will analyzed via the paired samples *t*-test, whereas differences between the groups will be compared via the independent samples *t*-test. If data is in skewed distribution, nonparametric test will be applied to perform within-group or between-group comparison. Statistical significance is defined as a *P*-value less than .05.

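### The order of the two moxibustion sessions is not described as randomised or balanced and no period term is named, so comparisons across sessions could be confounded with visit order

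*Protocol article*

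**What the plan says.** The sample size section gives 120 participants in three equal groups ("the total number of participants is 120, and they will be divided into the COPD group, healthy control group, and healthy intervention group"), so the healthy intervention group has 40.

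Section 2.6.2 gives that group moxibustion on both meridians. The stated gap, "The washout period between the 2 moxibustion sessions is more than 1 day", implies that the same person attends both sessions. The sessions are listed as item 1, Heart, heated at HT3, and item 2, Lung: "Moxibustion in the Lung meridian: moxibustion is applied at acupoint LU5 of the Lung meridian". The article does not say that this numbering is the visit order, and it mentions no random, balanced or fixed order. For the groups themselves, section 2.1 says only "Eligible participants will be divided into the COPD group, healthy control group, and healthy intervention group".

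Three sites are recorded in each session, with 5 minutes before, 15 minutes during and 5 minutes after moxibustion:

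- **Heart session:** Heart midpoint, Lung midpoint and LU5 ("The fNIRS probes will be attached to 3 measurement sites during moxibustion, including the midpoint of the Heart meridian along the left forearm").
- **Lung session:** Lung midpoint, Heart midpoint and HT3 ("The fNIRS probes will monitor oxygen saturation in 3 measurement sites synchronously during moxibustion").

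Section 2.11 plans that "change in continuous variables at different time points will be analyzed by repeated measures analysis of variance", with paired and independent t-tests or nonparametric tests and a significance level of .05. Time point is the only factor named. The Discussion predicts a larger change in the stimulated than in the non-stimulated meridian. It also lists the measures taken against confounding, and session order is not among them.

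**The concern.** This part of the study is a two-period crossover. Participants, operators and outcome assessors are all unblinded (section 2.5), and a second visit can differ from a first through familiarity with the heat, arousal or a residual effect of the earlier session. If everyone, or nearly everyone, has the same order, such a difference cannot be told apart from the difference between heating HT3 and heating LU5. The text as written allows that to happen, and order cannot be balanced once the data are collected.

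Comparisons across sessions matter here for two reasons. The Heart and Lung midpoints are different places on the forearm, so a difference within one session may reflect location rather than stimulation; separating the two needs both sessions. And LU5 is recorded only when HT3 is heated, and HT3 only when LU5 is heated, so any comparison of those two acupoints is a comparison across sessions.

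**Working it through.** **Inputs.** Group size: 120 / 3 = 40, which agrees with the stated 1:1:1 ratio. The 120 cannot be rebuilt, because it rests on precedent ("the sample size estimation is mainly according to similar trials") with no effect size, SD or power given; it is not disputed here. Alpha is 0.05, taken as two-sided because the article does not say. The documents give no period effect, so its size is an assumption throughout.

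**Notation.** Let y(s,m) be the change from the pre-moxibustion baseline in session s (H or L, the meridian heated) at the midpoint of meridian m (H or L). A shift in level that lasts through a whole session is already removed by that session's own baseline. What remains is a shift p in the *change*, at the second visit.

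**Step 1: cross-session contrast at one midpoint.** Take y(L,L) − y(H,L). With Heart always first, its mean is the true difference + p, so the bias is p. For a paired t-test with n = 40, the critical value on 39 df is 2.023 and the noncentrality is p × √40, with p in SDs of the paired difference. With no true difference:

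| Assumed p (SD) | Noncentrality | False-positive rate |
|---|---|---|
| 0.1 | 0.63 | 9% |
| 0.2 | 1.26 | 23% |
| 0.3 | 1.90 | 46% |
| 0.5 | 3.16 | 87% |

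With 20 participants per order, the mean is the true difference + p in one sequence and the true difference − p in the other. Their average has no bias. In simulation (4,000 runs) the period-adjusted test rejected about 5% of the time.

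**Step 2: same-session contrast.** Take y(L,L) − y(L,H). A shift p common to both sites enters both terms and cancels. In simulation the bias was about 0 and the rejection rate about 5% under either order.

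**Step 3: session effect at one site only.** Suppose the second-visit shift is 0.3 SD at the Lung site alone. The Lung-session contrast then has bias 0.30 SD and 45% false positives under a fixed order. Balancing the order only halves this, to 0.15 SD and 15%, because half the participants still have the Lung session second.

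**Step 4: contrast combined over both sessions.** For each participant take D = {[y(L,L) − y(L,H)] + [y(H,H) − y(H,L)]} / 2. This is the stimulated-by-measured-meridian interaction. A fixed difference in heat response between the two sites enters the brackets with opposite signs and cancels. A common period shift cancels within each bracket. For the Lung-site-only shift of 0.3:

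- **Fixed order:** the bias is 0.3 / 2 = 0.15. With independent changes of equal variance, scaled so that one bracket has SD 1, D has SD 1/√2 = 0.707. The standardised bias is 0.15 / 0.707 = 0.212, the noncentrality 0.212 × √40 = 1.34, and the false-positive rate about 26%.
- **20:20 order, adjusted for sequence:** the bias is +0.15 in one sequence and −0.15 in the other, so it averages to 0, with about 5% false positives.

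**Step 5: carry-over at the previously heated meridian.** If session 1 leaves an effect c in the change at the meridian it stimulated, that meridian is the non-stimulated one in session 2. D is then shifted by −c/2 in both sequences. Balancing does not remove this. It does give first-visit data under both stimulations, which carry-over cannot reach and against which it can be checked.

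**The case against.** The strongest reply is that the article is silent on order rather than wrong about it. List numbering describes what is done at each acupoint, not which visit comes first. The flowchart, schedule table and procedure figure are not visible, and a condensed article may leave sequence to the full protocol and a period term to a statistical analysis plan. This stands to the extent that a reader might infer that all 40 take Heart first, and the documents do not support that. It does not remove the point: the article gives the washout, probe sites, room conditions and a list of confounding controls in detail, but nothing on order.

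The second reply is that the stated hypothesis compares stimulated with non-stimulated meridians, and both midpoints are recorded together, each with its own baseline. This also stands, as Step 2 shows. A reader might infer that the whole moxibustion comparison is confounded, or that the trial's error rate is 23% to 87%; neither follows. Those rates need a fixed order, a shift in the change from baseline, and a test across sessions, which the article does not clearly plan. Nor can one speak of an acupoint compared when heated and when not, since neither acupoint is recorded while it is heated.

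Third, the washout, the 15-minute stabilisation, the controlled room and the similar time of day all limit session differences. They make a large shift less likely. They do not deal with familiarity or unblinded expectation at a second visit.

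**Conclusion.** The point holds in a limited form. Both sessions are given to the same people, no method for setting their order is described, and the named analyses contain no period term. The stimulated-versus-non-stimulated contrast within a session is safe from a session effect shared by both sites. Contrasts across sessions, and any contrast exposed to a site-specific session effect, are confounded with visit order if the order is fixed or unbalanced.

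The size is unknown, because the documents give no period effect. The calculated rates are illustrations that rest on n = 40, two-sided 0.05, a fixed order and assumed shifts; the 26% for the combined contrast also assumes independent changes of equal variance. The change is worth making because it is nearly free beforehand and impossible afterwards.

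**What to change.** 1. State the session order. Randomise the 40 healthy intervention participants 20:20 to Heart-first or Lung-first from a concealed, blocked list.
2. Name as primary the stimulated-minus-non-stimulated meridian contrast at the midpoints, in change from the pre-moxibustion baseline, combined over both sessions (the stimulated-meridian by measured-meridian interaction).
3. Include period in any analysis that uses both sessions. For the primary contrast, this means comparing D with sequence as a factor, equivalent to a period-by-measured-meridian term, since a period main effect cancels from D.
4. Use the pre-moxibustion recordings of the second session and the first-visit data to look for carry-over, which balancing alone does not remove (Step 5).
5. Say whether any direct Heart-session versus Lung-session comparison, or LU5 versus HT3, is intended, and label it secondary.

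The cost is an allocation list and about one degree of freedom in each test (39 to 38). No visits or participants are added.
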